### Study interventions

Patients starting with a standard APD regimen will receive treatment with 12 L of dialysis fluid (Dianeal 1.36% glucose) over 9 h (see Fig. 2a). The patient will then, within 4 weeks (1 − 28 days), receive an optimized APD regimen using 7 × 2 L of 2.27% Dianeal during 280 min followed by 5 × 2 L 0.1% glucose fluid (Certesol 0/3.5, Rivero) during 200 min (see Fig. 2b) (lactate-based fluid for continuous hemodialysis/hemodiafiltration). The dwell times for the optimized regimes should theoretically be varied depending on the transport type, but for simplicity, the dwell times have been set fixed in accordance with the above treatment times. This means that the total time under treatment will be approximately 8 h for the optimized regime. Patients will be in the supine position throughout the study protocol session time. Samples of dialysate will be collected from all drained bags (including the initial rinse), immediately after instillation of the first cycle and directly after instillation of the post-treatment rinse dwell.

**Fig. 2 Fig2:**
[figure not shown]
Intra-peritoneal volume as a function of treatment time in hours for **a** a standard 9 h 6 × 2 L 1.36% regime (dwell time 71 min) vs. **b** an modified optimized 7 × 2.27% + 5 × 0% APD regime (dwell time 20 min)

### Primary outcome

The primary outcome in the study is the amount of glucose (in grams) absorbed from the dialysate during the treatment (glucose absorption).

### Secondary outcomes

Secondary outcomes are osmotic water transport (“UF”), sodium removal, Kt/V urea, Kt/V creatinine, and incidence of complications up to 14 days post-intervention.

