### Study design

We will be conducting a randomized single-center, investigator-initiated, prospective, open-label study of two different APD regimens. The study is approved by the regional ethical vetting board in Córdoba, Argentina (Health ministry document registry number 3788), and will be conducted at the Hospital Privado Universitario in Córdoba. Overviews of the trial design according to the Standard Protocol Items: Recommendations for Interventional Trials (SPIRIT) statement and an overview of patient flow through the study are presented in Table 1 and Fig. 1, respectively. A SPIRIT checklist is provided in a supplemental file. A member of the research team will obtain informed consent non-consecutively from eligible participants. The length of the study will be from signing of informed consent until 30 days after the start of the first treatment session. A study investigator will follow all patients in a visit at the trial center. All patients will be evaluated with regard to potential adverse effects by one of the investigators.

**Table 1 Tab1:** Overview of enrolment, interventions, and assessments according to the SPIRIT (Standard Protocol Items: Recommendations for Interventional Trials) statement

	Study period							
	Recruitment	Allocation	Post-allocation					Close-out
Time point	−t_1_	0	t_1_	t_2_	t_3_	t_4_	t_5_	t_6_
Recruitment								
► Eligibility	**x**							
► Informed consent	**x**							
► Allocation		**x**						
Interventions								
► Optimized APD				**x**	**x**			
► Standard APD				**x**	**x**			
Assessments								
► 4 h D/P creatinine		**x**						
► Urea DV		**x**						
► Glucose absorption				**x**	**x**			
► UF and NaR				**x**	**x**			
► Blood chemistry			**x**	**x**	**x**	**x**		
► Physical examination			**x**	**x**	**x**	**x**	**x**	
► Kt/V urea+crea				**x**	**x**			
► Adverse events				**x**	**x**	**x**	**x**	**x**

*DV* distribution volume, *D/P* dialysate-over-plasma concentration ratio, *UF* net drained volume, *NaR* sodium removal, *Kt/V* calculated from net urea removal divided by plasma urea concentration and DV

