### Post-allocation exclusion criteria

After allocation, patients may be excluded due to in-trial peritonitis, catheter malfunction, inability to successfully complete both APD regimens, or the clinical judgment of the treating physician not to include the patient.

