### Randomization and blinding

Consenting patients that fulfill the inclusion criteria and meet no exclusion criteria will be randomized by the investigators using a random number generator to start treatment with either the standard APD or optimized APD regime. A priori we expect no difference in who receives which treatment first. Allocation concealment will be performed using a sealed opaque envelope.

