### Statistical analysis plan

The study will continue until a total of 20 patients have been included. This number is higher than that estimated in the power analysis. However, only patients who successfully completed both treatment regimens will be included in the analysis. Due to the complicated technical nature of the experimental setup, there may be a significant amount of unusable results, and the relative over-recruitment is aimed at compensating for a high post-allocation exclusion rate. The investigating team will perform the statistical analyses. In general, (1) analysis will be performed on a per-protocol basis, (2) all hypothesis tests will be paired and two-sided, with a maximal type I error risk of 0.05 ,and (3) imputation will not be used to correct for missing data in the analysis.

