### Publication plan

This study is registered in the ClinicalTrials.gov database (NCT04017572). Following completion of the trial, the manuscript will be submitted to a peer-reviewed journal, regardless of the trial outcome. For publication of the main outcomes, the first figure presented will be a Consolidated Standards of Reporting Trials (CONSORT) flowchart. The diagram will include the number of screened patients, the number of patients giving consent, the number of patients meeting all inclusion criteria, and the number of patients completing the protocol in each of the treatment groups. The second figure will depict glucose absorption for the respective treatments. The first table shall describe baseline variables as described above. The second table will describe secondary outcomes. Authorship will be granted according to the criteria described by the International Committee of Medical Journal Editors.

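### The complication outcome can lose events: the completer-only analysis makes no exception for it, and its 14-day window does not fit before the day-30 close-out when the sessions are 17 to 28 days apart

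*Protocol article*

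**What the plan says.** All places are in the protocol article.

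- **Outcome** (Secondary outcomes): "incidence of complications up to 14 days post-intervention". The section does not say whether the 14 days run from each session or only from the last.
- **Spacing** (Study interventions): "The patient will then, within 4 weeks", given there as 1 to 28 days, receive the other regimen.
- **Close-out** (Study design): a patient's participation lasts "until 30 days after the start of the first treatment session".
- **Order** (Randomization and blinding): patients are randomised "to start treatment with either the standard APD or optimized APD regime".
- **Exclusions** (Post-allocation exclusion criteria): "After allocation, patients may be excluded due to in-trial peritonitis, catheter malfunction", and also for not completing both regimens or on the treating physician's judgement.
- **Analysis set** (Statistical analysis plan): "only patients who successfully completed both treatment regimens will be included in the analysis", and "the relative over-recruitment is aimed at compensating for a high post-allocation exclusion rate".
- **Reporting** (Publication plan): "The second table will describe secondary outcomes". No separate presentation of complications is mentioned.
- **Recording** (Study design, Harms): all patients are evaluated for adverse events, which are entered in the case report form.
- **Special status** (Analysis of outcomes): if the primary outcome is negative, every other outcome becomes exploratory except the number of complications.

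**The concern.** Two stated rules work against a stated outcome. The completer rule suits glucose absorption, which needs a usable measurement under both regimens. Applied to complications, it selects on the outcome itself: in peritoneal dialysis, peritonitis and catheter malfunction are obvious complications, and here they are also grounds for leaving the analysis. Separately, three fixed time limits (14 days of observation, up to 28 days between sessions, closure at day 30) cannot all be met at every permitted spacing.

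The Background section says the pilot is meant to evaluate clinical safety. One regimen instils a fluid made for continuous haemodialysis into the peritoneal cavity, and there is no data monitoring board. With about 20 patients few events are to be expected, so one or two events lost or placed under the wrong regimen would visibly change the reported table.

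**Working it through.** The protocol gives no figure of its own for complications, so there is none to reproduce. The power calculation concerns glucose absorption and is not at issue.

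**1. Analysis set**

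- *A complication stops a session or prevents session two.* The patient has not completed both regimens. The completer sentence removes the patient, with no discretion.
- *Peritonitis or catheter malfunction occurs, but both sessions are completed.* The exclusion criteria allow removal but do not require it.
- *Is there an exemption?* The only one, in Analysis of outcomes, concerns whether complications are called exploratory. It does not change who is analysed. The Harms section ensures recording and reporting to authorities but sets no analysis set.

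An event can thus be in the case report form and absent from the analysed outcome.

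**2. Timing**

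Inputs: window 14 days, gap g = 1 to 28 days, closure at day 30, session one on day 0. The gap is worded for patients who start with the standard regimen; I assume it applies to both orders.

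- Days of the second window lost after closure: max(0, g + 14 − 30) = max(0, g − 16)
- Days of overlap if each session has its own window: max(0, 14 − g)

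| Gap (days) | Overlap | Lost after day 30 | Second window observed |
|---|---|---|---|
| 1 | 13 | 0 | 14 of 14 |
| 7 | 7 | 0 | 14 of 14 |
| 13 | 1 | 0 | 14 of 14 |
| 14 to 16 | 0 | 0 | 14 of 14 |
| 17 | 0 | 1 | 13 of 14 |
| 21 | 0 | 5 | 9 of 14 |
| 28 | 0 | 12 | 2 of 14 |

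- **Either reading of the window:** truncation at gaps 17 to 28, so 12 of 28 (43%).
- **Window per session only:** overlap at gaps 1 to 13 as well, 13 of 28. Together 13 + 12 = 25 of 28 (89%) are affected, and only 14, 15 and 16 are clean. If the session day and day 14 both count, gap 14 also overlaps and 26 of 28 are affected.
- **Window after the last session only:** no overlap, but the outcome then gives no comparison by regimen.

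These are shares of permitted gaps, not of patients.

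**3. Range for the days lost**

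The actual gaps are not given. If all were 16 days or less, nothing would be lost; if all were 28, 12/14 = 86% of second-window days would be. Assuming gaps uniform over 1 to 28, the loss is (1 + 2 + … + 12)/(28 × 14) = 78/392 = 19.9%. With onset uniform over the first 7 days it is 15/196 = 7.7%, and over the first 3 days 1/84 = 1.2%.

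**The case against.** The best defence is that no event goes unrecorded. Adverse events are evaluated in all patients, Table 1 schedules them through close-out, and they are reported to the review board and regulator. The completer sentence sits among remarks about unusable results from a technically difficult set-up, the per-protocol principle carries a general qualifier, and a safety set is often left to a fuller document. Part of this stands: data collected up to day 30 exist, and a safety listing could show them. But recording is not analysis, and it does not reach events after closure. The qualifier introduces the numbered list that follows; the completer sentence precedes it and is unqualified. The objection here is to that stated rule, not to a missing safety set.

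A reader might also infer more than the documents support:

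- *That most permitted spacings are faulty and the contrast between regimens is diluted.* This needs a window per session, which the protocol does not state.
- *That a true difference keeps only about 67% of its size.* This needs windows per session, uniform gaps, onset uniform over 14 days and attribution to the most recent regimen. With onset uniform over 7 or 3 days, about 85% or 96% is kept. None of these inputs is in the document.
- *That up to 10 of 20 patients could be unanalysed.* The Abstract closes the study at 20 completers, whereas the Statistical analysis plan section counts 20 included. The number outside the set is not fixed.
- *That the optimized regimen is favoured.* Order is randomised, so truncation and overlap fall on both regimens alike on average. No direction is shown for the exclusions either.

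**Conclusion.** The point holds as a risk of undercounting a safety outcome. The completer rule removes any patient whose complication prevents completion, and discretionary exclusion can remove others. The 14-day window cannot be observed in full at 12 of 28 permitted gaps, whichever way it is read. If the window applies to each session, only gaps of 14 to 16 days are free of both overlap and truncation, and events in an overlap cannot be assigned to one regimen.

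The number of events affected is unknown. It depends on the actual gaps, onset times and use of the exclusion criteria, none of which is given. The glucose absorption analysis is not affected. The rule is worth changing because complications are the one outcome the protocol protects from exploratory status.

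**What to change.** - **Analysis set:** report complications for every patient who started a session, by regimen received, exempt from the post-allocation exclusions and the completer rule. Keep the per-protocol set for glucose absorption.
- **Window:** state that it runs 14 days from each session. Where still possible, follow patients to 14 days after session two, at latest day 28 + 14 = 42.
- **Overlap:** list events in overlapping windows separately as not attributable to one regimen, and give the days observed per regimen. Simply assigning them to the most recent regimen would leave the cross-attribution in place.

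**Cost:** one or two sentences on analysis and reporting, and at most 42 − 30 = 12 more days of follow-up per patient. Trial status expected recruitment to be completed by March 31, 2020, before the article appeared. For patients already closed out, only the analysis and reporting rule can change: events already recorded can be restored to the outcome, but days after day 30 that nobody observed may not be recoverable.

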### Measurements

The weight of all bags of dialysis fluid, connectors, and drain bags will be carefully recorded before and after treatment start to assess the amount of fluid instilled and removed from the patient. The glucose, urea, creatinine, albumin, total protein, chloride, and sodium concentration of the effluent as well as the fresh dialysis fluid will be measured using the local hospital laboratory*.*

### Data collection and management

All study data will be recorded in case report forms (CRFs) for each patient, which are kept at the study site. Information on co-morbidities, medications, and routine laboratory analysis results will be collected from the hospital electronic chart system. The inclusion criteria will be registered in CRFs before allocation. All members of the research team have unlimited access to study data. The CRFs will be checked continuously during the study period by the study investigators to detect deviations from protocol.

### Sample size and power analysis

Published relative standard error values for glucose absorption comprise values ranging from 10 to 30% with a mean of 18% [3]. The worst performance for the optimized regime is a reduction in glucose absorption of about 10 g. Thus, a Monte Carlo-based power analysis was performed by the generation of 10,000 random samples *S* and *O* of size *N* from two normal sampling distributions having *μ* = 44 g; *σ* = 7.74 and *μ* = 34 g; *σ* = 5.94. The theoretically expected difference will differ depending on transport type and is higher with a faster peritoneal membrane. A Wilcoxon rank-sum test was performed to assess the statistical difference between the samples *S* and *O*. The statistical power was calculated as the number of significant (*P* < 0.05) results, for example, 8687/10,000 implies a statistical power of ~ 87%. The procedure was repeated by step-wise increasing *N* until a statistical power of > 80% was attained, which occurred at *N* = 10. For *N* = 20, the statistical power was found to be > 98%.

### Statistical analysis plan

The study will continue until a total of 20 patients have been included. This number is higher than that estimated in the power analysis. However, only patients who successfully completed both treatment regimens will be included in the analysis. Due to the complicated technical nature of the experimental setup, there may be a significant amount of unusable results, and the relative over-recruitment is aimed at compensating for a high post-allocation exclusion rate. The investigating team will perform the statistical analyses. In general, (1) analysis will be performed on a per-protocol basis, (2) all hypothesis tests will be paired and two-sided, with a maximal type I error risk of 0.05 ,and (3) imputation will not be used to correct for missing data in the analysis.

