## Background

In peritoneal dialysis (PD), the peritoneum of the patient is used as a biological dialyzer membrane by filling and draining the peritoneal cavity with dialysis fluid at pre-determined time points. Excess water is removed from the patient by osmosis, which is usually induced by the presence of high concentrations of glucose in the dialysate. The patient absorbs a significant amount of this glucose. In the light of the growing number of diabetic patients on PD, this unwanted glucose absorption is problematic and often represents a clinical challenge. A recent meta-analysis indicated that around 50% of PD patients may develop a glucose disorder which can significantly increase mortality [1].

Automated peritoneal dialysis is PD performed with the aid of a machine, a cycler, which aids the patient or the caregiver from the tedious work of filling and draining the PD fluid. Novel cyclers allow the treatment to be varied in a multitude of ways and recently, it was shown, using a theoretical model, that automated peritoneal dialysis could be improved by using a modified “bi-modal” treatment regimen in which exchanges using no osmotic agent is alternated with short “UF exchanges” having an osmotic agent [2]. Especially, it was shown that the potentially harmful glucose absorption could be reduced by 20–30%. Thus, the potential benefits of the novel regimens appear to be substantial.

The current pilot study aims to evaluate the clinical safety and feasibility of such optimized regimens in a small study using the HomeChoice Pro cycler. Since HomeChoice does not support exchanges having different lengths, the treatment will be divided into a “UF-part” comprising all the UF cycles and a “Clearance part”. A nurse will supervise the treatment and switch between the two parts manually. Moreover, as 0% glucose PD fluid is not available, a 0.1% glucose hemodialysis (CRRT) fluid will be used. We will use 2.27% glucose (Dianeal) for the UF exchanges.

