### Analysis of outcomes

Study outcomes will be analyzed using a Wilcoxon rank-sum test. A non-parametric test was chosen since such tests are more robust to outliers, which can have undue influence on the results of a parametric test for a small number of patients. In the event of no difference between the groups with regard to secondary outcomes and a difference in the primary outcome (glucose absorption lower in the optimized group), we will interpret such results as supporting our hypothesis but that confirmatory studies are needed using a higher number of patients since the low *N* in the current study may not be adequately powered to detect differences in the secondary outcomes. In this situation, a Monte Carlo-based sensitivity analysis will be performed to quantify the minimal difference needed to yield a significant difference in the secondary outcomes.

In the case of both a significant difference between the groups with regard to secondary outcomes and in the primary outcome (with glucose absorption lower in the optimized group), we will interpret these results as supportive of our hypothesis if the difference in secondary outcomes implies an improvement. Indeed, due to stirring effects, the higher DFR associated with the optimized regimes may result in improved NaR, urea, and creatinine clearance and UF [2]. In any other case, the differences will be compared to the differences expected theoretically according to the extended 3-pore model [2].

Should the primary outcome be negative or show a higher glucose absorption for the optimized regimen, then, all other outcomes are regarded as exploratory, with the exception of number of complications, and no emphasis will be placed on any differences between the treatment groups.

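### The completers-only analysis rule does not exempt complications, so their analysed incidence may be understated

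*Protocol article*

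**What the plan says.** All places are in the protocol article.

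- Background gives the purpose: "The current pilot study aims to evaluate the clinical safety and feasibility of such optimized regimens".
- Secondary outcomes lists "incidence of complications up to 14 days post-intervention".
- Analysis of outcomes gives complications a special status. If the primary outcome is negative, the other outcomes become exploratory, "with the exception of number of complications, and no emphasis will be placed on any differences between the treatment groups".
- Post-allocation exclusion criteria: "After allocation, patients may be excluded due to in-trial peritonitis, catheter malfunction, inability to successfully complete both APD regimens", with the treating physician's judgment as a further ground.
- Statistical analysis plan: "only patients who successfully completed both treatment regimens will be included in the analysis". The same section adds, as general principles, that "analysis will be performed on a per-protocol basis" and that "imputation will not be used to correct for missing data in the analysis".
- Study design and Harms say that every patient is evaluated for adverse events and that these are entered in the case report form.

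No separate set is named for complications. Assessment of baseline variables, by contrast, refers to all included patients.

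**The concern.** Some of the reasons for leaving the analysis set are the events that the complications outcome should count. Peritonitis and catheter malfunction are complications of peritoneal dialysis, and inability to finish a regimen is a feasibility failure. If the completers rule is followed as written, incidence is estimated in a group selected partly for not having had such events.

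This matters more here than in a trial where safety is secondary. Safety and feasibility are the stated purpose of the pilot, and the complication count is the one outcome kept out of the exploratory label when the primary fails.

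Completion could also plausibly differ by regimen. The optimized regimen has 7 + 5 = 12 exchanges against 6, a manual switch by a nurse part-way through, and a hemodialysis fluid in place of a glucose-free peritoneal fluid that is not available.

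**Working it through.** **Step 1. Who is removed.** Reading the completers rule together with the post-allocation exclusion criteria:

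| Patient | Fate in the analysis |
|---|---|
| Cannot complete one of the two sessions, for any reason | Removed; the rule is unqualified |
| Complication after session 1 that prevents session 2 | Removed, as above |
| Peritonitis or catheter malfunction, both sessions completed | May be removed; the exclusion wording is permissive |
| Peritonitis after session 2 | Has completed both sessions; stays unless the discretion is used |
| Complication that neither stops a session nor prompts exclusion | Stays and is counted |

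The trial is open-label, so whoever uses the discretion knows the regimen. The investigating team also performs the analysis.

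**Step 2. The plan's own figures.** The article gives no complication rate and no exclusion rate, so there is no safety figure to reproduce. The related figure is the sample size: 10 patients for more than 80% power, and more than 98% power at 20. A simulation with the stated inputs (normal, means 44 and 34 g, SDs 7.74 and 5.94, two-sided rank-sum test at 0.05, 10,000 replicates) gives 76.4% at 9, 83.2% at 10 and about 99% at 20. The stated figures are reproduced, and this point does not touch them.

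**Step 3. Effect on incidence (assumed inputs).** Let p be the true complication risk and q the share of complications that lead to exclusion. Assume that other exclusions are unrelated to complications. Then

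incidence among completers = p(1 − q) / (1 − pq).

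| p | q = 0 | q = 0.5 | q = 1 |
|---|---|---|---|
| 5% | 5% | 0.025/0.975 = 2.6% | 0% |
| 10% | 10% | 0.05/0.95 = 5.3% | 0% |
| 20% | 20% | 0.10/0.90 = 11.1% | 0% |

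At p = 10%, the chance that 20 patients show at least one complication is 1 − 0.90^20 = 87.8%. The chance that at least one stays in the analysis at q = 0.5 is 1 − 0.95^20 = 64.2%.

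In counts, again assumed: if 2 of 20 patients had peritonitis and both were excluded, the analysis would show 0/18 (exact 95% interval 0 to 18.5%) instead of 2/20 = 10% (1.2 to 31.7%).

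**Step 4. Effect on the comparison of regimens (assumed inputs).**

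- Equal q. True risks of 2% and 10% differ by 8 points. At q = 0.5 they become 0.01/0.99 = 1.0% and 5.3%, a difference of about 4.3 points. At q = 1 the difference is 0.
- Unequal q. Take a true risk of 5% under both regimens, with q = 0 under one and q = 0.5 under the other. The analysed risks are 5.0% and 2.6%, a false difference of about 2.4 points in favour of the regimen whose complications more often lead to exclusion.

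Incidence is therefore biased downward, while the comparison can move either way.

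**The case against.** The completers sentence was probably written with the dialysate measurements in mind. The reason given beside it is the technical complexity of the set-up and the unusable results this may produce. The per-protocol principle is introduced as a general one. Analysis of outcomes likewise assigns all study outcomes to one rank test, which suits continuous measures and not an incidence. Adverse events are evaluated and recorded in all patients and go to the review board and the regulator. The publication plan promises a flowchart with the number completing in each treatment group. A full analysis plan, not shown here, might define a safety set.

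Much of this stands, and it limits what may be claimed. Three readings that a reader might infer go too far:

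- *The trial would report no complications.* This holds only if every complication leads to exclusion. Removal for peritonitis or catheter malfunction is discretionary, and some complications stay in the set.
- *The plan conceals harms.* Collection and reporting of adverse events cover all patients.
- *The high exclusion rate that the article expects shows that many complications would be lost.* The article ties that rate to technical difficulty and unusable results, not to complications.

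The objection does not remove the point. Recording an event does not place it in the analysis of the secondary outcome. The completers sentence stands before the general principles and carries no qualifier. It is a stated rule, not a detail left to another document. The flowchart gives no undertaking to show reasons, and in a crossover its treatment groups may be sequences and not the regimen that failed.

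**Conclusion.** The point holds in limited form. As written, the analysis set excludes all non-completers and allows removal of patients with peritonitis or catheter malfunction, with no exemption for the complications outcome. The analysed incidence of complications may therefore be understated.

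The size cannot be derived from the article. For assumed true risks of 5% to 20%, the analysed incidence would be 2.6% to 11.1% if half of complications led to exclusion. These figures are illustrations, not forecasts. The direction of bias between regimens is not assured, because it depends on whether the excluded share differs by regimen. Glucose absorption, the primary outcome, and the sample size are outside this point.

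**What to change.** Amend the Statistical analysis plan section as follows:

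1. Restrict the completers set to glucose absorption, ultrafiltration, sodium removal, Kt/V urea and Kt/V creatinine.
2. Analyse complications and adverse events in all randomised patients who started at least one session, by regimen received. Sessions may be 1 to 28 days apart and complications are followed for 14 days, so the follow-up windows can overlap. State in advance to which regimen an event in an overlap is assigned.
3. Report non-completion with its reason, per session started and by regimen, as the feasibility result.

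The cost is a few sentences. Adverse events are already entered in the case report form for all patients. The sample size, the primary analysis and patient care do not change. The reason for each uncompleted session should be recorded if the form does not already ask for it.
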